## Abstract

Patients with chronic kidney disease (CKD) on hemodialysis (HD) experience treatment-related immobility and physical deconditioning, which is responsible for an increased risk of frailty and a high burden of multi-morbidity. Exercise has been shown to counteract this vicious cycle; however, its effectiveness has only been investigated in small cohorts. Therefore, the objective of the Dialysis Training Therapy (DiaTT) trial will be to assess the effects of a 12-month intradialytic exercise program on physical functioning, frailty and health economics in a large cohort of HD patients in a real-world setting. DiaTT will be a prospective, cluster-randomized (1:1), controlled, multi-center, interventional clinical trial across 28 dialysis units, aiming at the recruitment of >1100 CKD patients on HD. The intervention group will receive 12 months’ intradialytic exercise (combined aerobic and resistance training), whereas the usual care group will not receive intervention. The primary endpoint will be a change on the sit-to-stand test (STS60) result between baseline and 12 months. Secondary endpoints will include physical functioning, frailty, quality of life, 3-point MACE, hospitalizations, survival, quality of HD, health literacy and health care costs. By including almost as many patients as previously investigated in smaller trials, DiaTT will be the largest randomized, controlled trial assessing frailty, quality of life and mortality in the field of nephrology.

## 1. Introduction

Many patients with chronic kidney disease (CKD) suffer from marked deconditioning, leading to a vicious cycle of inactivity and a further decline in physical functioning [1]. The prevalence of frailty in patients with CKD ranges from 7% in community-dwellers (CKD Stages 1–4) to 73% in cohorts of patients treated with hemodialysis (HD) and has a direct impact on increased morbidity and mortality [2]. This was also observed in the Dialysis Outcomes and Practice Patterns Study (DOPPS, n = 7226, mean age 63.6 ± 14.4 years, median follow-up 17.2 months, self-reported functional status) [3], which showed that a very high proportion of dialysis patients, independent of age, experience difficulties in the performance of routine daily tasks and that low physical functioning was strongly associated with low quality of life and increased mortality [3,4].

Exercise training has been shown to counteract the decline of physical functioning in CKD. In a recent meta-analysis of fifty studies including n = 1757 CKD patients on HD, aerobic intradialytic training improved peak exercise capacity (VO_2_peak) by 2.07 mL/kg/min and 6-min walk test distance by 65 m [5]. Adding resistance to aerobic endurance training was even more effective, increasing VO_2_peak by 5.41 mL/kg/min [5]. Similar findings were reported in a meta-analysis of 27 studies including 1156 participants, showing that exercise programs, regardless of modality, generally increased physical performance parameters, such as sit-to-stand time or repetitions [6]. However, up to now, randomized trials of exercise interventions during HD have only included smaller cohorts, e.g., up to n = 228 patients [7], and the majority have tested interventions only for a short duration, e.g., 12 weeks [8]. Only very few studies evaluated longer intervention periods up to 9 months [7]. Moreover, a number of barriers to the implementation of exercise routines have been identified [1]. These include the widespread skepticism of dialysis staff towards exercise programs during dialysis, questions surrounding the suitability of very sick patients for exercise and the fear that exercise programs may interfere with the carefully orchestrated care processes of dialysis units and cause additional workload. In addition, patients treated with dialysis report a number of barriers to exercise, including hospitalizations, pain, fatigue and others.

However, contrary to this skepticism, in our experience of routine practice as well as our pilot study (46 HDpatients, age 63.2 ± 16.3 years, observation period up to 5 years), a supervised intradialytic exercise program, combining resistance and aerobic training twice weekly for 60 min, significantly improved exercise capacity, strength, quality of life and physical functioning and was associated with a high adherence rate of 78% after 1 year and 43% after 5 years, without safety issues [9]. Exercise was conducted by exercise therapists and did not require the involvement of the regular dialysis staff; it allowed the participation of patients with almost all clinical conditions or levels of disability and was found to integrate well with care processes in the dialysis unit.

The same concept will be applied in the current DiaTT trial, in which we will extend this experience from a single center to a multi-center context and substantially expand patient numbers, applying as few medical restrictions on participation as possible. By including only patients from one non-profit dialysis provider, the established dialysis structure, clinical assessment, clinical chemistry and data handling will be identical for all sites. The primary objective will be to assess the effectiveness of exercise training during HD compared to usual care (UC; no intervention) after 12 months. The intervention will combine strength and aerobic exercise training and add health literacy counselling (HLC). We will investigate clinical outcomes, such as frailty, morbidity, mortality and health economics, in order to facilitate the future implementation of intradialytic exercise into routine health care reimbursement, a request that has been made repeatedly by the nephrological community [6,10,11,12]. 

By including >1100 well-documented CKD patients in this large randomized study, the DiaTT trial, after completion, will be one of the three largest randomized, controlled trials comparing exercise intervention with the usual care in medicine, together with the HF ACTION trial, which included 2331 chronic heart failure patients over 30 months [13] and the Look AHEAD trial, which included 5145 obese patients with type 2 diabetes over 9.6 years [14]. 

## 2. Experimental Design and Methods

### 2.1. Study Design

DiaTT will be an interventional, cluster randomized (1:1), multicenter, controlled trial. After screening of dialysis centers and patient recruitment, 28 centers will be cluster randomized to IG or UC, as depicted in Figure 1. The randomization of centers will be stopped once a minimum of n = 1100 patients have been recruited. The intervention will consist of 12 months’ combined exercise training (aerobic and resistance), initiated after the baseline visit (V1), compared to UC without intervention.

The primary endpoint will be a change in the Sit-to-Stand (STS60) test result [15] from baseline to 12 months between groups. Secondary endpoints will include physical functioning (Timed-Up-and-Go test (TUG)), the Six-Minute Walk test (6MWT), the Grip Strength Test (GST)), frailty (Multidimensional Prognostic Index (MPI)), quality of life (SF-36), 3-point Major Adverse Cardiovascular Events (MACE), hospitalizations, overall survival, quality of HD (measured as serum phosphate and other laboratory values), medication (phosphate binders, erythropoietin), health literacy (HLS-EU-Q16 Health Literacy Questionnaire) and health economics (total costs of medication, hospitalization, therapeutic remedies, transportation, medical assistance tools, nursing care and sick leave from workplace). 

The study has been registered at ClinicalTrials.gov NCT03885102.

### 2.2. Center Eligibility 

The trial will be conducted in up to 28 dialysis centers of the non-profit kidney care provider KfH in Germany (Kuratorium für Dialyse und Nierentransplantation e.V.; Board of Trustees for Dialysis and Kidney Transplantation). Centers in the federal states of Saxony-Anhalt, Thuringia, North-Rhine Westphalia and Bavaria will be informed and, if interested, screened according to the following inclusion criteria: willingness to accommodate the training program in their center, adequate space for training and the storage of equipment and a minimum of n = 50 HD patients. Centers with an existing exercise program during HD will be excluded from participation.

### 2.3. Cluster Randomization of Centers

Participating centers will be randomly assigned to IG or UC using stratified block randomization with a block size of two centers and stratified by region. To ensure concealment, two centers from the same stratum will be randomized at the same time. 

### 2.4. Study Population

All patients from the participating dialysis centers will be asked to participate in the trial during the screening visit (V0). 

The inclusion criteria for CKD patients will be: age ≥ 18 years, chronic ambulatory HD for >4 weeks, written and signed confirmation by the treating dialysis physician that the patient is able to exercise, signed informed consent to participation on the Quality-in-Nephrology (QiN) registry, signed informed consent obtained according to confidentiality and data protection regulations, international guidelines and local laws. 

The exclusion criteria will be: unstable angina pectoris, uncontrolled arterial hypertension (systolic blood pressure > 180 mmHg or diastolic BP > 105 mmHg on repeated measurements), uncontrolled tachycardia, acute severe infection, planned live kidney transplantation within the next 12 months, planned conversion to home-HD or peritoneal dialysis within the next 12 months, long overnight dialysis, participation in a regular exercise program during HD sessions (≥1/week) in the last 6 months. 

Irrespective of the randomized center group assignment, all dialysis and other medical treatment procedures will follow standards of care and center routine without adaptations to the training intervention. Patients of both sexes will be enrolled and no study-specific sex distribution is foreseen. Patients who are hesitant about exercising because of their medical conditions or disabilities will be reassured and encouraged to participate, as long as their condition does not meet the exclusion criteria.

## 3. Procedure

### 3.1. Intervention and Usual Care Groups

#### 3.1.1. Usual Care 

Patients will receive general information on the importance of physical activity, nutrition and exercise opportunities, which are available to patients on dialysis under current health insurance laws and regulations. Routine dialysis care will continue according to local standards and practices without modification. 

#### 3.1.2. Intervention Group (IG)

In the IG, patients will participate in a standardized and individually adapted intradialytic exercise training program, supervised by specially trained exercise therapists. Patients will additionally receive HLC by the exercise therapists while exercising. The exercise intensity will be increased monthly according to standard operating procedures and reassessed every three months. Exercise therapists will continuously promote adherence and motivation to exercise intervention. 

The intervention will consist of a combined exercise program (aerobic and resistance training) thrice-weekly during HD. Each exercise session will last 60 min, with a short break between exercise modes (30 min cycling and 30 min of resistance training). The exercise training will be performed within the first two hours of the HD session. 

##### Aerobic Training

All aerobic exercises and tests will be performed on a bed-cycle ergometer in a semi-recumbent position, which adapts workload to the continuously monitored target heart rate (MOTOmed letto2, Reck-Technik GmbH & Co KG Medizintechnik, Betzenweiler, Germany) and has been previously used in patients with CKD for intradialytic training [9]. If needed, an electric support while pedaling can be programmed to engage weaker patients in cycling. 

The target heart rate (HR) will be determined by the Karvonen formula [HR_Training_ = (HR_max_ − HR_rest_) × Factor + HR_rest_] at baseline and on the six-month visit. Endurance training will start with a load of 2, 6, or 12 watts (according to the patient’s physical status) and increase stepwise until voluntary or symptom-limited exhaustion. The training should be perceived as moderately strenuous (Borg Scale of perceived exertion: 12–13, “somewhat hard”). The training intensity will increase every four to eight weeks by recalculating the target heart rate using a factor of 0.5 for the first month and a factor of 0.75 at month 5. After six months of training, HR_Training_ will be reassessed and the intensity will again increase stepwise by increasing the target heart rate using factors from 0.65 to 0.75. Thus, individualized training parameters will be programmed on a patient´s ergometry-ID card to facilitate an adaptive response by the cycle ergometer based on HR during training. The training data recorded by the ergometer will be regularly uploaded to the study database (eCRF). 

##### Resistance Training

Resistance training will be comprised of eight exercises for upper and lower limbs performed with dumbbells and elastic bands of varying resistance, as well as core strength exercises, in a semi-recumbent position. Exercises will be modified in accordance with patients’ functional status and disabilities (e.g., limb amputation) and adapted from previous experience [9].

Strength tests will be performed every three months to determine the one-minute maximum repetition rate for each exercise. The training intensity will be derived from these tests to achieve a perceived exertion of 12–13 (“somewhat hard”) on the Borg scale and will increase each month by increasing the number of repetitions, weight or resistance, according to standardized protocols. Exercises will be performed in two sets of one minute each with a one-minute break. Biceps and triceps are trained with weights (dumbbells) of 0.5, 1, 2, 4 or 7 kg. For the abductors, elastic bands (Theraband^®^) with different resistances will be used; rubber balls of varying sizes will be used to support adductor and core strength exercises. If the number of repetitions exceeds 50 per minute, the next heaviest load will be applied. Strength training data will be recorded by exercise therapists on training logs at every session and entered into the study database (eCRF). 

In general, patients are advised to increase their daily physical activity on non-dialysis days, based on their individual physical functioning and caregiving level. Physical functioning levels are defined as low (no standing or walking possible), moderate (standing and guided walking is possible) or high (free standing and walking). Instructions for the exercises will be provided by their local exercise specialists. Patients will be advised to use common household items such as water bottles, cushions, chairs walls, benches and handrails.

##### Health Literacy Counseling

During or after the exercise sessions, the exercise therapists will give short topic presentations of five minutes each, covering nutrition/diet, fluid intake, physical activity, hypertension, diabetes, atherosclerosis, smoking, alcohol and stress. Topics will be rotated every few weeks and presented in lay language, structured around four topic headers (relevance, symptoms, treatment, pointers). They will be accompanied by leaflets with graphics, aiming to educate and empower patients regarding their disease and lifestyle choices.

Health literacy will be assessed in all patients at baseline and after twelve months using the European Health Literacy Questionnaire (HLS-EU-Q16) [16].

### 3.2. Visit Schedule

Patients in eligible centers will be informed (in writing and orally) and screened for eligibility at V0. Two dedicated members of the study staff will conduct the screening visits in all centers to ensure the consistent communication of study-related information and recruitment. After written informed consent is obtained, centers will be randomized to either IG or UC, respectively. Patients will undergo baseline examinations (V1) three months after screening (V0), after a roll-out phase for the delivery of exercise equipment and the recruitment of local exercise therapists at intervention sites. Clinical assessments and tests of physical functioning will be performed at V1 and repeated at 3, 6, 9 and 12 months (Visits 2–5). For details about the assessments see Table 1. 

To ensure consistency, only a dedicated group of specifically trained exercise therapists will conduct the assessments of physical functioning.

The documentation assistants in the dialysis units will receive specific training by geriatricians to administer MPI. Routine care parameters, which are recorded continuously in the digital patient registry (KfH-QiN), will be summarized automatically for each study visit and transferred to the eCRF.

Data on health economics will be derived from the participating patients who are insured at one of the three collaborating German health insurance companies (Techniker Krankenkasse, BARMER or AOK PLUS). 

### 3.3. Risk-Benefit Assessment

The risk of the exercise intervention for the patients in the current trial can be considered low, because of the close monitoring and supervision during HD by the dialysis staff and trainers. In our pilot study, no serious adverse events (SAEs) related to intradialytic exercise were noted [9], which was consistent with findings in previous trials from other groups [7]. 

### 3.4. Adverse Events and Serious Adverse Events 

The following adverse events (AE), potentially linked to intradialytic exercise, will be recorded throughout the study: venous needle displacement or catheter disconnection during HD symptomatic hypotension during HD (clinically symptomatic, requiring medical intervention) and episodes of cramping (calves) during HD (requiring medical intervention). 

The following serious adverse events (SAE) will be recorded on the eCRF regardless of their occurrence during or between HD sessions: hospitalization (admission or discharge diagnosis) and death, including date and cause of death.

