### 4.3. Safety

Exercise training during HD is generally considered safe if general precautions are followed [22,26]. This includes patients with a wide range of disabilities and comorbidities. Therefore, in DiaTT, we will apply only minimal restrictions on participation because of acute, uncontrolled conditions and adapt the exercise programs based on individual baseline exercise capacity, comorbidities and disabilities, such as amputations. The intensity, duration, repetitions and/or load of exercises will be gradually increased. In addition to regular dialysis staff, exercise therapists will be present during the exercise sessions. Adverse events that are possibly related to exercise (hypotensive episodes, leg cramping, disconnection/dislodging of catheters/dialysis needles) and hospitalizations/deaths (SAEs) will be recorded to analyze safety of intradialytic training compared to UC [11].

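### Non-serious harm is recorded only as three dialysis-session events, so the planned comparison can support a safety statement for those events, admissions, deaths and MACE, but not for the whole exercise programme

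*Protocol article*

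**What the plan says.** Section 3.4 of the protocol article introduces its adverse events as an enumeration: "The following adverse events (AE), potentially linked to intradialytic exercise, will be recorded throughout the study". Three items follow:

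- "venous needle displacement or catheter disconnection during HD";
- symptomatic hypotension during a session, if it needs medical intervention;
- calf cramps during a session, if they need medical intervention.

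The serious adverse events are hospitalisation, with its diagnosis, and death, with its date and cause. These "will be recorded on the eCRF regardless of their occurrence during or between HD sessions".

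Section 4.3 names the same three event types plus hospitalisations and deaths, and says that they "will be recorded to analyze safety of intradialytic training compared to UC". Neither section mentions a category for other events.

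Sections 2.1 and 3.7.4 add hospitalisations, overall survival and 3-point MACE (cardiovascular death, non-fatal stroke, non-fatal myocardial infarction) as secondary endpoints.

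The intervention reaches beyond the dialysis session. Under Resistance Training in section 3.1.2, "patients are advised to increase their daily physical activity on non-dialysis days", with exercises taught by the local exercise specialists and done with household objects such as chairs, benches and handrails.

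**The concern.** The adverse event list is narrower than the intervention. Every non-serious item on it is tied to the dialysis session, and two of the three also require medical intervention. The programme includes resistance work that progresses each month, with dumbbells up to 7 kg and elastic bands, and taught activity on days without dialysis. No listed adverse event can occur on such a day.

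Section 3.3 rests its low-risk judgement on supervision during haemodialysis. The activity at home lacks that supervision, and it is also the part with no non-serious event recording.

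What is at stake is the reach of the eventual safety statement. The trial is meant to inform reimbursement (section 1) and guidelines (section 5), in a population for which section 1 reports frailty of up to 73% in haemodialysis cohorts. A strained shoulder, a fall at home without admission, or chest discomfort that ends a session could affect tolerability and adherence, yet would not appear in the comparison as described.

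**Working it through.** No figure in the plan bears on this point, so there is none to reproduce. The check is to trace each kind of event through the recording routes that the article describes.

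| Event | Listed AE (3.4) | SAE (3.4) | MACE (3.7.4) |
|---|---|---|---|
| Needle or catheter displacement in a session | yes | if admitted or fatal | no |
| Hypotension or calf cramp in a session, needing intervention | yes | if admitted or fatal | no |
| Fall, fracture or muscle or joint injury, admitted | no | yes, with diagnosis | no |
| Same, not admitted | no | no | no |
| Myocardial infarction, stroke, cardiovascular death | no | if admitted or fatal | yes |
| Chest pain or arrhythmia, admitted | no | yes, with diagnosis | only if infarction |
| Same, not admitted and not a MACE | no | no | no |

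Two rows have no route: falls and injuries without admission, and cardiac symptoms without admission or MACE.

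**Other data sources in the article**

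- The KfH-QiN registry supplies routine care parameters (section 3.2).
- Claims data come only from patients of three insurers and are planned for costs, hospital days and sick leave (sections 3.2 and 3.7.5).
- The session log holds strength training data, and the ergometer uploads hold training data (section 3.1.2).

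None is described as capturing falls, injuries or the reason a session was stopped.

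**Illustration of size.** All rates here are assumptions, because the documents give none.

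- Intervention patients: 1100 / 2 = 550, assuming the two arms of centres are about equal in size.
- Share with a fall or musculoskeletal injury from the programme: 2% to 10%, so 550 × 0.02 = 11 to 550 × 0.10 = 55 patients.
- Share of these admitted: 5% to 30%.
- Captured as SAEs: from 11 × 0.05 = 0.55 to 55 × 0.30 = 16.5 patients.
- Without a listed place: from 11 × 0.70 = 7.7 to 55 × 0.95 = 52.25, about 8 to 52 patients.

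The range shows only that the gap could matter at modest rates. It is not an estimate.

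**The case against.** The strongest reply is that the plan uses targeted recording for a low-risk intervention and that this is a legitimate choice. The serious end is well covered: admissions and deaths are recorded in both arms, with diagnosis or cause, on dialysis and non-dialysis days. Section 4.3 speaks of intradialytic training, and the list matches that scope. Training is semi-recumbent and supervised, so falls during sessions are unlikely, and the activity on other days is general advice adapted to function. The article condenses a fuller protocol, and the case report form is not shown.

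Much of this stands, and it rules out several stronger readings:

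- A reader might infer that falls, injuries and cardiac events cannot be counted at all. Those leading to admission or death are counted, and infarction and stroke are in the MACE endpoint.
- A reader might infer that the trial's safety conclusion is unsupported. The article draws none yet, and the planned data do support a comparison of the listed events. That these events also occur in usual care is no flaw, since the control arm exists to show any excess.
- A reader might take exclusion criteria such as "unstable angina pectoris, uncontrolled arterial hypertension" as an admission that training causes these harms. Section 2.4 uses them only to exclude unstable or uncontrolled patients.
- A reader might infer that sites have nowhere to enter other events. That is only an inference from the stated list.

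What the reply does not remove is the mismatch in scope. The article states the list twice and builds its safety comparison on it, so this is not a detail left open for the full protocol. Musculoskeletal injury and cardiac symptoms can arise in a semi-recumbent session, and the activity on other days is part of what intervention patients are taught.

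**Conclusion.** The point holds as a limit on what the recorded data can show. As written, non-serious falls, musculoskeletal injuries and cardiac symptoms without admission are outside the stated list, and no other source described in the article is shown to capture them. The planned comparison can support a statement about the three intradialytic events, admissions, deaths and MACE. It cannot support one about the programme as a whole, including activity on non-dialysis days.

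The number of events missed cannot be derived from the documents; the 8 to 52 patients rest entirely on the assumed rates. The primary endpoint and sample size are unaffected. This is an inexpensive improvement to safety data capture, not a contradiction or a wrong figure. It rests on reading the enumeration in section 3.4 as complete, which its repetition in section 4.3 supports. If the full protocol already has a category for other events, only the article's wording needs to change.

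**What to change.** 1. In section 3.4, add falls, fractures, and musculoskeletal injury needing treatment or a pause in activity. Ask about them with the same questions, in both arms, at each quarterly follow-up visit (V2 to V5). Identical questioning matters because intervention patients see therapists at every session, and spontaneous reports would be biased towards that arm.
2. Add a reason-for-early-stop field to the session log that therapists already keep, with options for chest pain, arrhythmia, blood pressure and injury. Report it descriptively, because usual care has no comparator.
3. In section 4.3, limit the safety statement to the events actually recorded.

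The cost is a few items at visits that already take place and one field on an existing log, with no new procedure or staff. Section 3.5 gives the documentation assistant the data not related to the exercise intervention. Falls and injuries asked of all patients can fit that role if worded as general health events, and session stops stay with the therapists. The downside is slightly more data entry and a possibly less favourable adverse event table. The change concerns data capture only and leaves the exercise prescription and patient management untouched.
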